*Exclusion Criteria for Participants*. Patients would be excluded if they met one of the following criteria.Patients with one of the following diseases: (1) acute valvular heart disease; (2) pericardial disease; (3) cardiomyopathy; (4) congenital heart disease; (5) acute myocardial infarction (AMI) within four weeks; (6) cardiac shock; (7) acute myocarditis or serious arrhythmia with variation in hemodynamics.Patients who suffer from pulmonary artery hypertension caused by cor pulmonale, pulmonary embolism, or stroke within a half year.Patients who suffer from serious hepatic insufficiency (the index of liver function being 2 times the normal one), renal insufficiency (Ccr > 20%, Scr > 3 mg/dL, or 265 *μ*mol/L), diseases of blood system, malignant tumor, diabetes mellitus with serious complications, hyperthyrea, or hypothyrea.Patients who suffer from infection, fever, or patients meeting one of the following criteria: the numeration of leukocyte being more than 10 × 10^9^/L, the percentage of neutrophil granulocyte being more than 85%; patchy shadows in X-ray of chest.Pregnant women and women in lactation.Patients with mental disorders or related infections.Patients who took part in other trials within two months before the present study.

*Sample Size*. The sample size calculation is based on prophase clinical study (31 cases, 13 in CHM group and 18 in placebo group), standard deviation of experimental group (*S*
_*e*_) = 25.84718, standard deviation of control group (*S*
_*c*_) = 32.54499, mean of experimental group (${\bar{x}}_{e}$) = 39.07692, mean of control group (${\bar{x}}_{c}$) = 32.54499, and the number of control group (*c*) = 1. The following formula is used to calculate the sample size:(1)$$\begin{array}{c} n=\frac{{\left(\upsilon_{\alpha }+\upsilon_{\beta }\right)}^{2}\left(1+1/c\right)\sigma^{2}}{\delta^{2}}\\ \sigma^{2}=S^{2}=\frac{S_{e}^{2}+cS_{c}^{2}}{1+c}\delta^{2}={\left|{\bar{x}}_{e}-{\bar{x}}_{c}\right|}^{2}. \end{array}$$

The estimated number of subjects in each group was 98.18012, and 196.36024 subjects are needed in two groups. The number was increased to 215.18012 assuming a maximum dropout rate of less than or equal to 10%, and a total of 220 subjects were included (110 subjects in each group).

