*Randomization*. A total number of 220 participants were randomly assigned with a ratio of 1 : 1 to CHM or placebo group according to random number sequence. Stratified blocked randomization was taken to insure the balance of two groups.

*Blinding*. In this stage, the double-blind design was used. Drugs for CHM and placebo groups were prepared and provided by Beijing Kangren Tang Pharmaceutical Co., Ltd. (Beijing, China). In CHM group, drugs of four syndromes (qi deficiency, blood stasis, water retention, and yang deficiency) were prepared, while the placebo was provided in the same character, smell, and weight as the drugs for CHM group. Drugs of each syndrome were prepared as granules without decoction. The CHM drugs and placebo were numbered according to a random figure table which was blinded to both the doctors and the patients. Participants were provided with CHM or placebo based on their syndrome differentiation at the beginning and two weeks later. They took CHM or placebo twice per day for four weeks.

*Setting*. In this stage, participants were admitted into seven hospitals of four provinces in China: (1) Dongfang Hospital Affiliated to Beijing University of Chinese Medicine; (2) The Affiliated Hospital to Changchun University of TCM; (3) Guang'anmen Hospital Affiliated to China Academy of Chinese Medicine Sciences; (4) Hubei Provincial Hospital of TCM; (5) Wuhan Hospital of TCM; (6) Yichang Hospital of TCM; (7) Zhengzhou Hospital of TCM.

*Interventions*. According to the guideline for chronic heart failure [5], standardized western medicine treatment, such as angiotensin-converting enzyme inhibitors (ACEIs) or angiotensin-receptor blockers (ARBs), *β*-blockers, and diuretics, could be used for patients in CHM and placebo groups as basic therapy. The dosages of all medicines used are following the guideline for CHF [5].

The recipe for qi deficiency was composed of* Astragalus membranaceus* (Fisch.) Bge. var.* mongholicus *(Bge.) Hsiao (huangqi, 60 g) and* Codonopsis pilosula *(Franch.) Nannf. (dangshen, 15 g).

The recipe for blood stasis was composed of* Salvia miltiorrhiza *Bge. (danshen, 15 g),* Paeonia lactiflora *Pall. (chishao, 15 g),* Prunus davidiana* (Carr.) Franch. (taoren, 10 g), and* Carthamus tinctorius* L (honghua, 10 g).

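### The Stage Two sample size does not follow from its printed inputs: the control mean repeats the control SD, and formula (1) then gives about 318 per group at 80% power, not 98

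*Protocol article*

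**What the plan says.** The Stage Two sample size (protocol article, section 3.1.2, Sample Size) rests on a pilot of "31 cases, 13 in CHM group and 18 in placebo group". The paragraph lists four pilot statistics in a row, and each label is followed by its value:

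- Experimental SD: "25.84718, standard deviation of control group"
- Control SD: "32.54499, mean of experimental group"
- Experimental mean: "39.07692, mean of control group"
- Control mean: "32.54499, and the number of control group"

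It then prints formula (1), a two-sample comparison of means with c = 1, and reports: "The estimated number of subjects in each group was 98.18012, and 196.36024 subjects are needed in two groups". For losses it adds: "The number was increased to 215.18012 assuming a maximum dropout rate of less than or equal to 10" per cent, and rounds up to 220, or 110 per group. Patients are "randomly assigned with a ratio of 1 : 1 to CHM or placebo group".

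The paragraph gives neither alpha nor power. The Statistical Analysis paragraph of the same section sets a two-tailed 0.05 level. Power is stated nowhere.

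**The concern.** A mean and an SD from 18 patients would hardly agree to seven digits, so one of the two entries for 32.54499 is probably a copy of the other. These numbers set the planned effect and the size of the trial, and the article reports the result to five decimals, so it should be reproducible from what is printed.

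If it is not, a reader cannot tell whether Stage Two was planned for a difference of about 6.5 or for one nearly twice as large. Section 3.1.3 makes Stage Three conditional on CHM beating placebo in Stage Two. A null Stage Two result would mean something quite different at 38% power than at 80%.

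**Working it through.** **Inputs.** From the Sample Size paragraph: Se = 25.84718, Sc = 32.54499, experimental mean 39.07692, control mean 32.54499, c = 1. From the Statistical Analysis paragraph: two-sided 5%. Power is assumed to be 80%, with a range shown.

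**Formula (1) with the printed inputs**

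- σ² = (25.84718² + 32.54499²)/2 = 863.63, so σ = 29.39
- δ = 39.07692 − 32.54499 = 6.53193
- (1 + 1/c)σ²/δ² = 2 × 863.63/6.53193² = 40.483
- n per group = 40.483 × (u_α + u_β)²

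| Level | Power | n per group |
|---|---|---|
| two-sided 5% | 70% | 250 |
| two-sided 5% | 80% | 318 (40.483 × 7.849 = 317.7) |
| two-sided 5% | 85% | 364 |
| two-sided 5% | 90% | 426 |
| one-sided 5% | 80% | 251 |
| one-sided 5% | 90% | 347 |

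The plan's 98.18012 is not reproduced. At two-sided 5% and 80% power the required n is 317.7/98.18 = 3.2 times the stated n.

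**What 98.18 would imply.** u_α + u_β = √(98.18012/40.483) = 1.557. This is below 1.96, so at the two-sided 5% level the implied power is under 50%:

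- at 98.18 per group: Φ(1.557 − 1.96) = 0.34
- at 110 per group: √(110/40.483) = 1.648, and Φ(1.648 − 1.96) = 0.38

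**Variants tried.** Two unusual set-ups come near 98 without reaching it. One-sided 10% with 60% power gives 95.4. One-sided 5% with 80% power, using only the experimental variance and dropping the factor (1 + 1/c), gives 96.8. Neither fits the two-sided 5% level, and the second also departs from formula (1).

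**Which entry is likely wrong?**

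- *If the SD were the copy* and the mean correct, 98.18 at two-sided 5% and 80% power would need σ² = 98.18012 × 6.53193²/(2 × 7.849) = 266.85. Then Sc² = 2 × 266.85 − 25.84718² = −134, which is impossible.
- *If the mean is the copy*, solving for δ with (1.96 + 0.84)² = 7.84 gives δ = √(2 × 863.63 × 7.84/98.18012) = 11.744, so the control mean is 39.07692 − 11.744 = 27.33.
- *Whole sums.* 39.07692 × 13 = 508.000 is a whole number, as expected if the pilot values were recorded as integers. 32.54499 × 18 = 585.81 is not. A sum of 492 gives 492/18 = 27.333, δ = 11.744 and n = 98.19.

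**Dropout.** 196.36024/0.9 = 218.18 and 196.36024 × 1.1 = 216.00. The plan prints 215.18012. The 220 recruited covers either figure.

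**The case against.** The strongest reply is that this is a typing slip and the trial is correctly sized. The back-calculation supports that: with a control mean near 27.33, 98 per group gives 80% power, and then 318, 34% and 38% do not describe the trial. That is the likelier reading, but it is inference. It takes two-sided 5% and 80% power for granted, the whole-sum check assumes integer data, and some whole sum over 18 patients always lies close to any target mean. The match is also not exact: 492/18 gives 98.19 with rounded normal deviates and 98.30 with 7.849, against 98.18012. The value 27.33 should therefore be treated as a hypothesis for the pilot data to settle.

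Four further points deserve an answer:

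- *318 depends on an unstated power.* True, so the range of 250 to 426 belongs beside it. The failure to reproduce 98.18 does not depend on that choice.
- *The variable behind the pilot figures is not named.* This stands. The primary outcome is LVEF and entry requires LVEF of at most 40%, so a baseline SD could not exceed about 20 points, and SDs of 26 and 33 do not fit. The planned analysis is also repeated-measures ANOVA, not the comparison in formula (1). The 34% and 38% are therefore power for the printed difference under formula (1), not established power for LVEF.
- *Stage Two is complete, according to the Trial Status note.* This limits the remedy to a restatement, but the stated basis for the trial's size is still wrong as printed.
- *The dropout slip is under one patient or three, depending on the convention.* Agreed; it is minor.

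**Conclusion.** The concern holds. The control mean duplicates the control SD, and formula (1) with the printed inputs does not give 98.18 per group at the stated two-sided 5% level with any conventional power. Taken at face value, the inputs require about 318 per group at an assumed 80% power, and the recruited 110 per group gives about 38%. If the mean is a misprint for about 27.33, the size of 98 per group is sound for 80% power, but the planned difference is about 11.7, not 6.5. The second explanation is more likely, though the document cannot confirm it. Until the pilot mean and the power are given, the planned effect and the power of the trial are unknown to the reader. The inflated total of 215.18 is a separate error without consequence for the 220.

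**What to change.** In the Sample Size paragraph of section 3.1.2:

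1. Replace the control mean with the value from the pilot data, and name the variable that the pilot statistics describe.
2. State the alpha, sidedness and power used (apparently two-sided 5% and 80%) and the resulting difference, then recompute n from formula (1).
3. If 32.54499 is in fact the pilot control mean, keep the 220 patients and restate the power for a difference of 6.53 as about 38% at 110 per group.
4. Correct the inflated total to 196.36/0.9 = 218.2 (or 216.0 if the ×1.1 convention was meant, and say so). Either is covered by 220.

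The cost is a look-up in the pilot data and a correction to one paragraph. No extra patients and no change in conduct are needed.

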#### 3.1.2. Stage Two

The second stage of this trial was a multicentral, randomized clinical trial with placebo-controlled and double-blind methods.  Figure 2 shows the trial flowchart. 

*Diagnostic Criteria*

*Diagnostic Criteria for CHF*. Diagnostic criteria were as follows: (1) diagnostic criteria of CHF:* 2007 China Guideline for the Diagnosis and Treatment of CHF* [5]; (2) heart function standard:* The Criteria for Diagnosis and Treatment of Heart Disease *first published by the New York Heart Association (NYHA) [11]. 

*Diagnostic Criteria for TCM Syndrome Differentiation*. Diagnostic criteria were as follows: TCM differentiation standard: according to the* Guiding Principles for the Clinical Study of New Drugs in Traditional Chinese Medicine* released in 2002 [12]. 

*Inclusion Criteria for Participants*. Patients who accorded with diagnostic criteria were potentially eligible for the study if they met the following criteria.The primary heart disease is CHD (with diagnosis for CHD confirmed by coronary angiography, coronary computed tomography, history of acute myocardial infarction, limb-salvage Q wave for electrocardiogram (ECG), ECG test, radionuclide examination support, etc.). The included patients should have no history of hypertension or taking antihypertensive drugs, with a blood pressure under 160/100 mmHg.With a history of CHD, the following symptoms and signs were observed: difficult breathing, fatigue, fluid retention (edema), left ventricular enlargement, systolic volume of left ventricular increase with LVEF ≤ 40%, and NYHA functional classification II or III.Male or female patients should be between 40 and 75 years old.If there was any violation of those criteria, the subject could not participate in this research.

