The recipe for water retention was composed of* Alisma orientalis *(Sam.) Juzep. (zexie, 10 g),* Polyporus umbellatus* (Pers.) Fries (zhuling, 15 g),* Plantago asiatica* L. (cheqianzi, 10 g), and* Descurainia sophia *(L.) Webb. ex Prantl (tinglizi, 10 g).

The recipe for yang deficiency was composed of* Cinnamomum cassia *Presl (rougui, 4.5 g) and* Aconitum carmichaelii *Debx. (zhifuzi, 10 g).

Table 6 lists the names of the CHM drugs in Chinese and English. All CHM herbs were verified by high-performance liquid chromatography (HPLC).

Patients in placebo group received placebo which was the same in shape, size, taste, weight, and package as CHM granules. CHM drugs and placebo were prepared as granules. Granules quality met internal control standards of Beijing Kangren Tang Pharmaceutical Co., Ltd. (Beijing, China), and complied with GMP (Good Manufacturing Practice) standards. Patients were treated with CHM or placebo granules twice per day for four weeks based on syndrome differentiation.

Participants were prohibited from taking other Chinese medicine during the treatment period.

The drugs for the treatment of hypertension (HBP), diabetes mellitus, dyslipidemia, and other diseases could be used reasonably. And the reason, name, and dosage should be recorded in detail.

*Outcome Measurements*. The primary outcome measure was left ventricular ejection fraction (LVEF). Secondary outcome measurements were 6-minute walk test (6MWT), traditional Chinese medicine syndrome scores, and New York Heart Association (NYHA) functional classification. Side effects were to be monitored during the trial period. Many biological indicators (blood routine examination, liver function, kidney function, and ECG) were tested before and after the treatment. The timeline of participants through Stage Two is shown in Table 4.

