*Statistical Analysis*. Data were analyzed on the Intention-to-Treat (ITT) analysis and the per-protocol set (PPS) for coherence. The basic characteristics were compared with independent samples *t*-test for continuous variables and chi-square analyses for categorical variables. Repeated-measure ANOVA was used for the evaluation of the primary and secondary outcomes. The measurement data were expressed as mean ± standard deviation for us to check the data of all groups with normal test and homogeneity of variance test. Results were shown with 95% confidence intervals (CIs). The level of significance was set at 0.05. If *P* < 0.05, there were statistical differences. All tests were 2-tailed.

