**Figure 3 fig3:**
[figure not shown]
The flowchart of Stage Three trial design.

**Table 1 tab1:** Databases search strategies.

Databases	Search terms
CNKI	[(Mesh terms = heart failure) OR (Title = chronic heart failure) OR (Keywords = chronic heart failure)] AND [(Mesh terms = syndrome) OR (Keywords = syndrome)]

CBM	(Mesh terms = chronic heart failure OR Mesh terms = CHF OR Mesh terms = chronic congestive heart failure OR Mesh terms = chronic cardiac insufficiency) and ((Mesh terms = syndrome) or (Mesh terms = traditional Chinese medicine))

VIP	((Title or keywords: chronic cardiac insufficiency) OR (Title or keywords: CHF) OR (Title or keywords: chronic heart failure) OR (Title or keywords: chronic congestive heart failure)) AND (Title or keywords: syndrome) AND (Title or keywords: symptom) AND (Medicine and health) AND (All Periodicals) AND (Year: 1994–2008)

**Table 2 tab2:** The distribution of symptoms in 176 literatures.

Symptom	Frequency	Rate (%)
Palpitation	233	5.6
Shortness of breath	160	3.9
Edema	159	3.8
Lassitude	153	3.7
Thread pulse	146	3.5
Dyspnea	126	3.0
Wheeze	117	2.8
Pale tongue	111	2.7
Intermittent pulse	110	2.7
Knotted pulse	110	2.7
Oliguria	101	2.4
Sweating	100	2.4

**Table 3 tab3:** The distribution of syndromes in 176 literatures.

Syndrome	Frequency	Rate (%)
Yang deficiency	6489	18.57
Qi deficiency	6377	18.25
Blood stasis	5731	16.40
Water retention	3445	9.86
Phlegm syndrome	973	2.78

**Table 4 tab4:** The timeline of participants' course through Stage Two.

Items	Baseline	Treatment	
	Visit 1	Visit 2	Visit 3
	0 weeks	2 weeks	4 weeks
Inclusion/exclusion	•		
Informed consent	•		
Grouping	•		
Medical history collection	•		
General information	•		
Medication history	•		
Physical examination	•		
Complicating diseases	•		
Drug release	•	•	
TCM syndrome scores	•	•	•
NYHA functional classification	•	•	•
6-minute walk test	•	•	•
LVEF	•	•	•
X-ray	•		
Routine urine test	•		•
Liver function test	•		•
Renal function test	•		•
Electrolytes	•		•
Electrocardiogram	•	•	•
Side effect		•	•

**Table 5 tab5:** The timeline of participants' course through Stage Three.

Items	Baseline	Treatment	
	Visit 1	Visit 2	Visit 3
	0 weeks	2 weeks	4 weeks
Inclusion/exclusion	•		
Informed consent	•		
Grouping	•		
Medical history collection	•		
General information	•		
Medication history	•		
Physical examination	•		
Complicating diseases	•		
Drug release	•	•	
TCM syndrome scores	•		•
NYHA functional classification	•		•
6-minute walk test	•		•
LVEF	•		•
X-ray	•		

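### Stage Two's single method, repeated-measures ANOVA for every outcome, suits ordinal NYHA class poorly and does not by itself deliver a week-4 treatment difference in LVEF

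*Protocol article*

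**What the plan says.** All references are to the Protocol article.

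- Section 3.1.2, Statistical Analysis, names one method for all efficacy outcomes: "Repeated-measure ANOVA was used for the evaluation of the primary and secondary outcomes". Of the analysis sets it says: "Data were analyzed on the Intention-to-Treat (ITT) analysis and the per-protocol set (PPS) for coherence". It also promises 95% confidence intervals and two-sided tests, and adds: "The level of significance was set at 0.05".
- Section 3.1.2, Outcome Measurements, makes LVEF primary. The secondary outcomes are the 6-minute walk test, "traditional Chinese medicine syndrome scores, and New York Heart Association (NYHA) functional classification".
- Section 3.1.2, Inclusion Criteria, limits entry to "NYHA functional classification II or III".
- Section 3.1.2, Randomization: "Stratified blocked randomization was taken to insure the balance of two groups".
- Table 4 ("The timeline of participants' course through Stage Two") schedules LVEF, 6MWT, TCM syndrome score and NYHA class at weeks 0, 2 and 4.
- Section 3.1.3 (Stage Three) has the same four efficacy outcomes. There the article splits the methods: a two-sample t-test on change from baseline to week 4 for measurement data, and chi-square for categorical variables. Stage Three runs only if the herbal treatment beats placebo in Stage Two, and its sample size is to be based on Stage Two LVEF.

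**The concern.** There are two separate issues.

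First, NYHA class is a coarse ordinal scale that can take only two values at entry. A normal-theory model for its mean treats the steps between classes as equal and the residuals as roughly normal. Neither is a natural assumption here.

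Second, a two-group, three-visit repeated-measures ANOVA of LVEF gives a group test, averaged over visits, and a group-by-time test on 2 degrees of freedom. Neither estimates the treatment difference at week 4, and a 2-df test has no single effect estimate to which the promised 95% CI could attach. If the method is run in its usual form, the pre-treatment value is one of the three responses, which pulls the averaged group effect towards zero. Patients with a missing visit also leave the analysis unless values are imputed.

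Stage Two decides whether Stage Three goes ahead and supplies its sample-size inputs. Both uses need a defined LVEF difference with a matching variance.

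**Working it through.** **NYHA.** Set the two stages side by side. Stage Two puts every primary and secondary outcome, hence NYHA class, under ANOVA. Stage Three, with the same outcomes, separates measurement data from categorical variables. The Stage Two sentence makes no such exception. This part needs no arithmetic.

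**LVEF.** The article gives no figure that depends on the repeated-measures analysis, so there is nothing to reproduce, and the figures below are illustrative.

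Inputs:
- 98 patients per group: the pre-dropout number in section 3.1.2, Sample Size (98.18), used only as a group size.
- Two-sided 5% level (section 3.1.2).
- Week-4 effect of 0.40 SD: assumption. It is the effect that a plain two-sample comparison at week 4 would detect with 80% power: (1.960 + 0.842) × √(2/98.18) = 0.40.
- Effects at weeks 0, 2 and 4 of 0, 0.20 and 0.40 SD: assumption. The alternative 0, 0.40, 0.40 follows below.
- Equal correlation ρ between visits, 0.3 to 0.8: assumption.
- Baseline included as a response in the two ANOVA tests: assumption (the conventional form).

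Formulas, in SD units:
1. Group main effect: z = ē / √[((1 + 2ρ)/3) × 2/98], where ē is the mean effect over the three visits. Here ē = (0 + 0.20 + 0.40)/3 = 0.20, half the week-4 effect.
2. Group-by-time: noncentrality λ = (98/2) × Σ(e − ē)² / (1 − ρ), chi-square on 2 df. Here Σ(e − ē)² = 0.08.
3. Week 4 adjusted for baseline: z = 0.40 / √[(1 − ρ²) × 2/98].

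At ρ = 0.6:
1. z = 0.20/0.1223 = 1.635, power Φ(1.635 − 1.960) = 37%.
2. λ = 49 × 0.08/0.4 = 9.8, power 81%.
3. z = 0.40/0.1143 = 3.50, power Φ(3.50 − 1.960) = 94%.

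| ρ | Group main effect | Group-by-time (2 df) | Week 4, baseline-adjusted |
|---|---|---|---|
| 0.3 | 48% | 55% | 84% |
| 0.5 | 40% | 71% | 90% |
| 0.6 | 37% | 81% | 94% |
| 0.7 | 35% | 91% | 98% |
| 0.8 | 32% | 98% | 99.7% |

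If the full effect is present by week 2 (0, 0.40, 0.40), ē = 0.267, two thirds of the week-4 effect. Main-effect power then runs from 72% down to 52% as ρ goes from 0.3 to 0.8. Interaction power runs from 69% to above 99%. The week-4 column is unchanged. At ρ = 0.7 the interaction (97%) and the adjusted week-4 test (98%) are almost equal.

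**Incomplete patients.** At the planned dropout ceiling, 0.10 × 220 = 22 patients could be incomplete, leaving 198. The power figures above use the pre-dropout group size, so they do not include any loss from deletion.

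**The case against.** The strongest reply is that the article names a method and says nothing about how it was set up. A reader might infer that baseline was treated as a response, that incomplete patients were dropped, that the strata were left out of the model, and so that the ITT commitment was defeated. None of this is stated. Baseline could be a covariate with weeks 2 and 4 as the responses, missing values could be imputed, and a full protocol or SAP, not shown, could specify all of it. This stands: those features belong to the usual form of the method and can only be raised conditionally.

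It is also right that dilution affects only the group main effect. The usual efficacy test in a design of this kind is group-by-time, which is not diluted and at high correlation comes close to the baseline-adjusted test. The 32% to 48% range is therefore the unfavourable reading and not a prediction.

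A reader might call ANOVA of NYHA class invalid. With about 100 patients per group a comparison of mean scores is not meaningless, so poorly suited is the fair description.

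Finally, the Stage Three inputs could be taken from the reported means and standard deviations, so the ANOVA does not block them. But the article does not make that week-4 difference the Stage Two result. None of these replies removes the NYHA mismatch, or the fact that neither ANOVA test is the week-4 comparison that Stage Three is built on.

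**Conclusion.** The point holds in a limited form. From the text alone, one method is assigned to all Stage Two outcomes. It is poorly suited to ordinal NYHA class and out of step with the article's own treatment of categorical variables in Stage Three. For LVEF at three visits, neither standard test from that method is a week-4 treatment difference.

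If baseline was a response, the group main effect estimates one half to two thirds of the week-4 effect, depending on whether the effect builds linearly or is complete by week 2. The interaction is not shrunk, but it generally has less power than a baseline-adjusted week-4 comparison: 55% against 84% at ρ = 0.3, and 98% against 99.7% at ρ = 0.8, for the linear pattern. If incomplete patients were deleted without imputation, up to 22 of 220 would fall outside the stated ITT analysis. All power figures rest on the assumed 0.40 SD effect, its time pattern and the correlation range, none of which the article gives.

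The documents do not support the stronger conclusion that the Stage Two LVEF result is biased or that ITT was abandoned.

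**What to change.** Analyse LVEF, 6MWT and TCM syndrome score at weeks 2 and 4 with a mixed model for repeated measures containing treatment, visit, treatment-by-visit, baseline value and the randomisation strata, using all observed data. Report the week-4 treatment contrast with its 95% CI. State how many randomised patients have no post-baseline value, since they contribute nothing to this model. Analyse NYHA class with an ordinal model, such as a cumulative logit, adjusted for baseline class.

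The Trial Status paragraph says that Stage Two is complete. These results should therefore stand beside the stated ANOVA, labelled as a revised post hoc analysis, and should not replace it. The report should also say how baseline and incomplete patients were handled in the ANOVA that was run.

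Use the week-4 LVEF difference and its variance as the Stage Three sample-size inputs. The variance must match the Stage Three test: that test is a t-test on change, with per-patient variance 2(1 − ρ) in units of the outcome variance, against 1 − ρ² after baseline adjustment. The smaller figure is appropriate only if Stage Three also adjusts for baseline.

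The cost is some extra analysis of data already collected, and the post hoc label.

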#### 3.1.3. Stage Three

If the efficacy of CHM on CHF is better than placebo in Stage Two, we will conduct Stage Three to evaluate the feasibility, compliance, and universality and make cost-effectiveness analysis of CHM on CHF based on syndrome differentiation. A flowchart of the third stage is shown in Figure 3.

*Diagnostic Criteria*

*Diagnostic Criteria for CHF*. Diagnostic criteria are the same as those of Stage Two.

*Diagnostic Criteria for TCM Syndrome Differentiation*. Diagnostic criteria were the same as those of Stage Two.

*Inclusion Criteria for Participants*. Patients who accorded with diagnostic criteria were potentially eligible for the study if they met the following criteria.The primary heart disease is CHD (with diagnosis for CHD confirmed by coronary angiography, coronary computed tomography, history of acute myocardial infarction, limb-salvage Q wave for electrocardiogram (ECG), ECG test, radionuclide examination support, etc.). The included patients also had no history of hypertension or taking antihypertensive drugs, with a blood pressure under 160/100 mmHg.With a history of CHD, the following symptoms and signs were observed: difficult breathing, fatigue, and fluid retention (edema), with left ventricular enlargement, along with increasing of left ventricular end systolic volume and LVEF ≤ 50%, with NYHA cardiac function II or III.Male or female patients should be between 40 and 75 years old.

If there is any violation of those criteria, the subject could not participate into this research.

*Exclusion Criteria for Participants*. Exclusion criteria were the same as those in Stage Two.

*Sample Size*. This design in this stage is to show the superiority of TCM based on syndrome differentiation. The ratio in this stage is 1 : 1. The sample size calculation is based on LVEF of Stage Two. To calculate the sample size, we will use the following formula (*δ* = 2):(2)$$\begin{array}{c} n=\frac{\left({\left(Z_{1-a/2}+Z_{1-\beta }\right)}^{2}*\left(\sigma_{1}^{2}+\sigma_{2}^{2}\right)\right)}{{\left(\varepsilon -\delta \right)}^{2}}. \end{array}$$

And the maximum dropout is 10%.

*Randomization*. All participants in this stage will be randomly distributed to CHM or placebo group according to random number sequence.

*Setting*. In this stage, five or more centers will take part in the trial.

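### Stage Two tests LVEF by a three-visit repeated-measures ANOVA with no stated week-4 contrast or baseline adjustment, so neither of its usual tests gives the week-4 difference that Stage Three needs

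*Protocol article*

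**What the plan says.** All references are to the protocol article.

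- Section 3.1.2, Outcome Measurements: "The primary outcome measure was left ventricular ejection fraction (LVEF"). No time point is attached.
- Section 3.1.2, Statistical Analysis: "Repeated-measure ANOVA was used for the evaluation of the primary and secondary outcomes". The ANOVA term that carries the test, the role of week 0 and a visit contrast are not given. The same paragraph promises ITT and per-protocol analyses and 95% confidence intervals.
- Table 4 ("The timeline of participants' course through Stage Two") marks LVEF at weeks 0, 2 and 4.
- Section 3.1.2, Sample Size, uses a formula for comparing two group means.
- Section 3.1.3 makes Stage Three conditional on CHM outperforming placebo in Stage Two, and says "The sample size calculation is based on LVEF of Stage Two". Its Statistical Analysis paragraph compares change from baseline to week 4 by t-test, and Table 5 has LVEF at weeks 0 and 4 only.

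**The concern.** Stage Two has to answer a directional question: is LVEF better on CHM than on placebo after four weeks, and by how much? A repeated-measures ANOVA with three visits offers two group tests. The group main effect averages all visits, and at week 0 randomised arms differ only by chance, so including it pulls the estimate towards zero. The group-by-time test asks only whether the two mean profiles are parallel.

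Two things are at stake. One is the decision to start Stage Three, which could turn on which p-value is read. The other is the LVEF effect carried into the Stage Three sample size, which should match the week-4 change analysed there. The article is specific about the week-4 change for Stage Three, so the mismatch lies in the method named for Stage Two and is more than an effect of condensing the protocol.

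**Working it through.** **The plan's own figure.** Section 3.1.2 gives SDs of 25.84718 and 32.54499, means of 39.07692 and 32.54499, and equal groups. Then σ² = (25.84718² + 32.54499²)/2 = 863.63 and δ = 6.532. With α from "The level of significance was set at 0.05" and "All tests were 2-tailed", and 80% power assumed because none is stated, n = (1.960 + 0.842)² × 2 × 863.63 / 6.532² ≈ 318 per group. The stated 98.18 is not reproduced. At 98 per group these inputs give about 34% power. That is a separate matter, but it means the 80% reference below is an assumption and not the plan's own power.

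**Inputs for the comparison.**
- From the article: 98 per group (rounded), two-sided α 0.05, LVEF at weeks 0, 2 and 4.
- Assumed: a week-4 effect that a plain two-sample comparison detects with 80% power, i.e. (1.960 + 0.842) × √(2/98) = 0.40 SD, with noncentrality 2.802² = 7.85; equal variances; a common between-visit correlation ρ of 0.5-0.8; a week-2 effect equal to k times the week-4 effect, with k from 0.5 to 1.

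**Dilution of the group main effect.** With week 0 as a level, the estimate is (0 + k + 1)/3 of the week-4 effect: 0.50 for k = 0.5 and 0.67 for k = 1.

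**Noncentrality λ.**
- Group main effect over three visits: λ = 7.85(1 + k)² / [3(1 + 2ρ)].
- Group-by-time, 2 and 388 df: λ = 7.85 × SS/(1 − ρ), where SS is the sum of squares of (0, k, 1) about its mean: 0.50 for k = 0.5 and 0.667 for k = 1.
- Week-4 ANCOVA with baseline as covariate: λ = 7.85/(1 − ρ²).

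Example, k = 0.5 and ρ = 0.5:
- Main effect: λ = 7.85 × 2.25/6 = 2.94. Power is Φ(1.716 − 1.960) = 40%.
- Group-by-time: λ = 7.85 × 0.5/0.5 = 7.85. Power from the noncentral F is 70.5%.
- ANCOVA: λ = 7.85/0.75 = 10.47. Power is Φ(3.235 − 1.960) = 90%.

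| ρ | k | Group main effect | Group-by-time | Week-4 ANCOVA |
|---|---|---|---|---|
| 0.5 | 0.5 | 40.3% | 70.5% | 89.9% |
| 0.5 | 1 | 62.8% | 83.1% | 89.9% |
| 0.7 | 0.5 | 34.7% | 90.8% | 97.5% |
| 0.7 | 1 | 55.1% | 96.9% | 97.5% |
| 0.8 | 0.5 | 32.4% | 98.3% | 99.7% |
| 0.8 | 1 | 51.8% | 99.7% | 99.7% |

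Against ANCOVA, the group-by-time test loses 7-19 points at ρ = 0.5 and 0-7 points at ρ of 0.7 or more. ANCOVA equals or beats both ANOVA tests in every row.

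**The case against.** The strongest reply is that the article does not say the group main effect is the test, nor that week 0 is a repeated level. Table 4 lists measurements, not model terms. Where baseline is a level, group-by-time is the usual test of differing change. It suffers no dilution and, at the correlations of 0.7 or more in the table, costs little power. All of this stands, so the one-third to one-half loss is conditional. Choice of term and follow-up contrasts may also be set out in an analysis plan not shown, so their absence alone is no fault.

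Three stronger inferences are tempting but unsupported:
- **Patients with a missed visit are discarded.** Classical ANOVA uses complete cases, but the article promises ITT and does not rule out imputation.
- **The type I error is inflated through non-sphericity.** This presumes an uncorrected test, which the article does not state.
- **Stage Three will be grossly mis-sized.** The article does not define ε in formula (2) or say that it is read from an ANOVA group effect. Its two arm-specific variances fit ordinary arm summaries at least as well.

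The reply does not supply the missing estimate. A significant group-by-time F can reflect a week-2 difference that has gone by week 4, its sign is not part of the test, and it provides no single difference on which to put the promised confidence interval.

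**Conclusion.** The point holds in conditional form and is worth acting on. The method named for the Stage Two primary outcome isolates no week-4 treatment difference under either of its usual group tests, although the Stage Three decision and analysis call for one.

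If the three-visit group effect is read, the estimate is 50-67% of the week-4 difference and power is about 32-63%, where a plain week-4 comparison would have 80%. If group-by-time is read, the weakness is mainly one of interpretation: power is 70-99.7% against 90-99.7% for ANCOVA, and close to it at correlations of 0.7 or more. These figures rest on the assumed 80% reference, correlation range, equal variances and week-2 fraction, none of which the article gives. A reader might infer that the Stage Two result is certainly diluted; the article does not establish that.

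**What to change.** Report the CHM-minus-placebo difference in LVEF at week 4, adjusted for baseline LVEF, with its 95% CI. Use either ANCOVA at week 4, or a mixed model with weeks 2 and 4 as outcomes, baseline LVEF as covariate, treatment, visit and treatment-by-visit terms, and a week-4 contrast. State which ANOVA term the existing analysis relied on and whether week 0 was a level in it.

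Use the week-4 estimate as the Stage Three effect, with the SDs that match the Stage Three analysis. If Stage Three keeps its t-test on change, these are the arm-specific SDs of change from baseline to week 4.

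The article says that Stage Two is complete. The new analysis must therefore be labelled as added after completion and shown beside the stated ANOVA, not put silently in its place. The cost is one re-analysis of data already collected, plus a sentence of explanation in the report and in the Stage Three sample-size section.
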